### **5.4. Randomization and Allocation**

Patients fulfilling the inclusion/exclusion criteria above will be randomized following consent in a 1:1 ratio. Permuted block randomization will be utilized in blocks of 8 patients. Allocation will be to one of two groups: 1) ERCP using ED34-i10T2 duodenoscope with DEC or 2) ERCP using a conventional duodenoscope (ED34-i10T). Confidential random number allocation will be accessed via a secure internet software. The study investigators, outcome adjudicators and patients will be blinded to allocation. The endoscopist will not be blinded. In cases where additional or alternate duodenoscope(s) is/are required to achieve the desired goal of the ERCP procedure, the choice(s) of device(s) will be left to the discretion of the endoscopist, regardless of the study arm to which the patient has been allocated.

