## **8. Study Period and Sequences**

### **8.1. Index Procedure**

Consecutive patients undergoing ERCP will be flagged as potentially eligible for study participation. On the day of the procedure, the patient will be approached by a research assistant (RA), who will explain the study, confirm eligibility, and answer any potential questions. If the patient agrees to participate, the relevant informed consent form is signed and witnessed. If the patient decides not to participate, the ERCP proceeds as per the usual standard of care, with or

without the use of DEC as per the endoscopist's discretion (and the sequence that follows does not apply).

1. The RA collects any relevant patient-related and pre-procedural data through combination of direct patient interview and review of the medical records.
2. The patient is randomized to one of the two study arms.
3. The patient enters the endoscopy/fluoroscopy room and the procedure commences.
4. During the ERCP procedure, relevant peri-procedural data are recorded by the RA by direct observation, and/or, if necessary, in consultation with the procedural physician(s) and/or nurse(s).
5. After the procedure is complete, the patient is moved to the recovery room for observation. Depending on their disposition and the course of the procedure, observation times and protocols differ. During this stage, the RA collects any relevant post-procedural data, and any missing pre- or peri-procedural data.
6. Any peri- or immediate post-procedural adverse event(s) is/are recorded.
7. The patient is examined by the endoscopist prior to discharge and provided with written post-procedure information, including a phone number to call in the event of any issues.
8. The RA meets with the patient prior to their discharge from the unit to answer any final potential questions.

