An exact test will be used to test the two-sided hypothesis that DEC is superior to control duodenoscopes in terms of persistent bacterial contamination. Using a power of 80% with a two-sided alpha of 0.05, 194 subjects in each arm will be required, for a total of 388 patients. To compensate for possible errors in sampling or loss of samples through transportation, an additional 10% of duodenoscopes will be sampled, for a **total of 426 subjects**. For the purposes

of the second co-primary objective of the study, the first 426 patients enrolled as part of the first co-primary objective will have their duodenoscopes sampled (213 from each arm). An anticipated 25% of the sample size will be recruited from Kingston.

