### C) ANALYSIS

Two-tailed Fisher's exact tests and chi-squared tests will be used to compare proportions. Outcomes will be compared between groups in an intention-to-treat analysis without adjustment. Comparisons will be reported using relative risks (RRs) and numbers needed to treat (NNTs) along with their respective 95% confidence intervals (CIs).

*Post hoc* subgroup analyses will be performed on sex (female or male), age (<65 or ≥65 years), study site (Calgary or Kingston), procedural complexity (1-2 or 3-4), papilla status (native

papilla or prior sphincterotomy), disposition (inpatient or outpatient), biliary stent placement (present or none), and indication (suspected or confirmed malignancy or all others). All statistical analyses will be performed using RStudio version 1.2.1335 (Integrated Development Environment for R, Boston, USA).

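### The trial has two centres, but no site stratification is stated and the SAP's co-primary contrasts ignore site: a modest loss that the analysis can still repair

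*Supplement*

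**What the plan says.** Section 4 of the current protocol names two referral centres, Calgary and Kingston. Section 9.1 adds: "An anticipated 25% of the sample size will be recruited from Kingston".

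On randomisation, section 5.4 says "Patients fulfilling the inclusion/exclusion criteria above will be randomized following consent in a 1:1 ratio" and "Permuted block randomization will be utilized in blocks of 8 patients". No stratification factor is named, and the section does not say whether there is one list or one per site. It also says "Confidential random number allocation will be accessed via a secure internet software". On blinding it says "The study investigators, outcome adjudicators and patients will be blinded to allocation" and "The endoscopist will not be blinded". The research assistant (RA) appears in neither statement.

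The RA's duties are described elsewhere. In section 8.1, "the patient will be approached by a research assistant (RA), who will explain the study, confirm eligibility, and answer any potential questions"; the RA then records data while watching the procedure. In section 8.2 the RA times the cleaning, a step in which any disposable cap is discarded.

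The SAP, under C) Analysis, states: "Outcomes will be compared between groups in an intention-to-treat analysis without adjustment". Study site (Calgary or Kingston) appears there once, in a list of post hoc subgroups. The data dictionary in part B has no site variable. Part A gives N = 422 for microbiology and N = 518 for technical success.

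**The concern.** Each hospital has its own scopes, reprocessing room, staff and endoscopists. Site is therefore a plausible predictor of both contamination after reprocessing and technical success. The 92% baseline success rate in section 9.1 comes from one centre's data, and no Kingston rate is given.

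In a two-centre trial one would expect randomisation stratified by site, an analysis that accounts for site, or both. Neither is stated here. What is at stake depends on how the lists were built:

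- **One shared list.** The arms can differ by chance in their share of Kingston patients, and an unadjusted contrast carries that imbalance.
- **One list per site.** The arms are balanced within site, but the analysis then ignores a factor used in the randomisation. A single fixed block size also makes some allocations predictable to anyone at that site who knows the size and sees past allocations.

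These are alternatives. They do not add up.

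**Working it through.** **1. The plan's own figures**

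- Technical success (92% in both arms, margin 7 points, one-sided 0.025, power 80%): n = 2 × (1.960 + 0.842)² × 0.92 × 0.08 / 0.07² = 235.8, so 236 per arm, as stated.
- Contamination (10% v 3%, two-sided 0.05, power 80%, pooled variance): 193.5, so 194 per arm, as stated.

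Neither calculation involves site.

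**2. If one list was shared: imbalance at Kingston**

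Inputs: N = 426 sampled, 213 per arm and a 25% Kingston share (section 9.1), so 0.25 × 426 ≈ 106 patients; blocks of 8 (section 5.4). Assumption: the two sites enrol in random order.

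- With a shared blocked list and Kingston share p, the variance of the Kingston arm difference is N p (1 − p) = 426 × 0.25 × 0.75 = 79.9, so the SD is 8.9.
- Simple randomisation would give √106 = 10.3. Blocking across sites helps a little but does not balance within site.
- Simulation of the shared list agrees: SD 8.9, median absolute difference 6, 95th percentile 18, and 20 or more in about 3% of trials.

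In a parallel simulation of all 520 patients (about 130 at Kingston), the 95th percentile is 19 with a shared list and 2 with a list per site.

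**3. Effect on the contamination contrast**

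Shift = site gap × Kingston arm difference / 213. The documents give no site-specific rates, so the gaps are assumptions.

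| Assumed site gap | Difference of 6 (median) | Difference of 18 (95th percentile) |
|---|---|---|
| 5 points | 0.14 points | 0.42 points |
| 10 points | 0.28 points | 0.85 points |

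The planned difference is 7 points. For technical success, with 260 per arm and a Kingston difference of 20 (just above the 95th percentile of 19), the shift is 20/260 × gap, or 0.4 and 0.8 points for the same gaps, against a 7-point margin.

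**4. Precision gained by stratifying the analysis**

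Put the within-site variance, 0.25 × pK(1 − pK) + 0.75 × pC(1 − pC), into the formula of step 1 (pK and pC are assumed success rates at Kingston and Calgary, averaging about 92%).

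| pK | pC | Gap | n per arm, stratified |
|---|---|---|---|
| 0.92 | 0.92 | 0 | 236 |
| 0.87 | 0.937 | 6.7 points | 233 |
| 0.82 | 0.953 | 13.3 points | 226 |

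Stratifying needs no extra patients, and the gain is small.

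**5. If lists were per site: predictability**

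For a block of 2m = 8 (m = 4), take an observer who knows the block size and sees every earlier allocation at that site.

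- Certain allocations per block: 2m/(m + 1) = 8/5 = 1.6, which is 20%.
- Best-guess correct calls per block: m + (4^m / C(2m, m) − 1)/2 = 4 + (256/70 − 1)/2 = 5.33, which is 66.6%.

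Under a shared list, with staff seeing only their own site, guessing against the running imbalance was right about 53% of the time at Calgary and 51% at Kingston in simulation. That is close to chance.

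**The case against.** The strongest defence is that the unadjusted analysis is valid. If randomisation was unstratified, chance imbalance by site is part of the sampling error that the test and confidence interval already cover. It has no direction and, at plausible site gaps, is small. The precision gain is also small. All of this stands. It limits the size of the point but does not remove it, because a site-stratified contrast uses data that the trial must already hold.

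A reader might infer three stronger things that the documents do not support.

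- **That site imbalance and guessable allocation both apply.** A large imbalance needs one shared list. The 20% and 66.6% figures need a list per site, knowledge pooled across sites, or a period when one site recruited alone. With a list per site and blocks of 8, the arms at a site can differ by at most 4.
- **That unblinded staff who confirm eligibility could select patients.** The only role named as unblinded is the endoscopist. That the RA knew past allocations is a fair inference from sections 8.1 and 8.2, but nothing says that the RA knew the block size. Allocation is confidential, web-based and after consent. Consecutive patients are invited, technical success has blinded duplicate adjudication, and the culture analysts are blinded.
- **That site was not recorded.** The SAP plans a Calgary/Kingston subgroup, so site must be available. Its absence from the dictionary is a gap in the listing.

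Changing the randomisation is also a weak remedy. Lists per site would raise local predictability, and varied blocks of 4, 6 and 8 remove certain calls but still allow about 68% correct guesses. The SAP's 518 and 422 patients, against 520 and 426 planned, suggest that enrolment is over.

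**Conclusion.** The point holds for the analysis. The plan describes a two-centre trial, states no stratification by site, and compares both co-primary outcomes without regard to site. The effect is modest. At the 95th percentile of imbalance under a shared list, the contamination contrast moves by about 0.4 points for a 5-point site gap and 0.8 for a 10-point gap. This rests on assumed site gaps, a 25% Kingston share and random interleaving of the sites. It does not invalidate the unadjusted test or change the required sample size. Predictable allocation remains conditional: up to 20% of assignments could be certain, but only with lists per site and an observer who knows the block size and sees past allocations. The documents do not settle whether those conditions held.

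**What to change.** Amend the SAP before the A/B arm codes, which its dictionary marks as blinded, are opened:

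1. Add a site variable to the dictionary.
2. Make both co-primary contrasts site-stratified, using a Mantel-Haenszel risk difference with its confidence interval. For technical success, compare the interval with the 7-point margin. Keep the unadjusted result as sensitivity analysis.
3. Report the arm-by-site table, whether there was one list or one per site, and who knew the block size. State the RA's blinding status in the same place.

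The cost is a few lines of SAP text and slightly more analysis work, for a small gain in precision and removal of chance site imbalance from the main contrasts. No new data are needed. Changing the randomisation settings is worth considering only if patients remain to be enrolled.

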## 7. Study Outcomes

### 7.1. Primary Outcomes

There are two co-primary outcomes for this study. The first primary outcome of the study is the **ERCP technical success rate** with the ED34-i10T2 duodenoscope and DEC, compared to the currently available duodenoscope (ED34-i10T). Technical success will be determined in duplicate by two blinded outcome adjudicators with no knowledge of the patient's allocation in the study. The adjudicators will review redacted and de-identified procedure reports for each study patient, and determine the presence or absence of technical success of the overall procedure based on a set of *a priori* definitions (see below). Any potential disagreements will be resolved by a third blinded adjudicator. Technical success will also be determined subjectively on a case-by-case basis by the endoscopist performing the procedure, in order to measure correlation with the adjudicator determinations, but not to be used in the determination of the co-primary outcome. Failure of the procedure due to inability to safely perform the procedure under conscious sedation will not constitute a technical failure for purposes of this study, in either study arm. The second co-primary outcome is the **persistent bacterial contamination rate** with the ED34-i10T2

duodenoscope and DEC, compared to the currently available duodenoscope (ED34-i10T) following standardized disinfection and reprocessing. This will be defined as:

- any growth of  $\geq 10$  colony-forming units (CFUs) at 72 hours, and/or
- any growth of one or more Gram-negative pathogen regardless of CFU count.

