### **7.1.1 Definitions of Technical Success**

Technical success will be dependent on the indication for the ERCP, as shown in Table 1. These definitions will be used by the blinded adjudicators to determine the presence or absence of technical success on a case-by-case basis.

Table 1. Definitions of Technical Success by ERCP Indication.

| Indication for ERCP                                                                                                                                                                                                                                                                                                                              | Definition(s) of Technical Success                                                                                                                                                                                                                                         |
|---------------------------------------------------------------------------------------------------------------------------------------------------------------------------------------------------------------------------------------------------------------------------------------------------------------------------------------------------------|-----------------------------------------------------------------------------------------------------------------------------------------------------------------------------------------------------------------------------------------------------------------------------------|
| Suspected or confirmed bile duct stone(s)                                                                                                                                                                                                                                                                                                               | Extraction of stone(s)

OR

CBD clearance based on absence of filling defects on occlusion cholangiogram

*If difficult biliary stones are encountered during procedure, use 'Difficult biliary stone(s)' indication below, and above definition does not apply |

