|                  |                                                                                 |                                                                                                                                                                                                                                                                                                       |
|------------------|---------------------------------------------------------------------------------|-------------------------------------------------------------------------------------------------------------------------------------------------------------------------------------------------------------------------------------------------------------------------------------------------------|
| ice_duo_ease_rn  | ease of use of overall scope design, according to assisting/cleaning nurse      | (scale from 0 to 10)                                                                                                                                                                                                                                                                                  |
| ice_duo_cross    | crossover to alternate scope design/ study arm                                  | 0 = no crossover; 1 = crossover                                                                                                                                                                                                                                                                       |
| age              | patient age                                                                     | (continuous)                                                                                                                                                                                                                                                                                          |
| sex              | patient sex                                                                     | 1 = female; 2 = male                                                                                                                                                                                                                                                                                  |

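### No rule says how a switch of duodenoscope is scored: as written, a DEC procedure completed with the control scope counts as a DEC success, which can bias the non-inferiority test towards success

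*Supplement*

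**What the plan says.** Five places bear on this point, in the latest protocol (the two-center version) and SAP v1.0.

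- **Protocol 5.4.** The text provides for a change of scope: "In cases where additional or alternate duodenoscope(s) is/are required to achieve the desired goal of the ERCP procedure". When that happens, the endoscopist decides freely which device to use, whatever the allocation. The provision covers both arms, and the endoscopist is not blinded.
- **Protocol 7.1.** The endpoint is introduced as the technical success rate "with the ED34-i10T2 duodenoscope and DEC, compared to the currently available duodenoscope (ED34-i10T"). The instruction to the adjudicators, who read redacted procedure reports, is to "determine the presence or absence of technical success of the overall procedure".
- **Protocol 7.1.1, Tables 1 and 2.** "Technical success will be dependent on the indication for the ERCP, as shown in Table 1". Neither the definitions of success nor the list of reasons for failure mentions a change of scope. The only special handling is that patients whose sole reason for failure is sedation are left out of the final analysis.
- **SAP section B.** The dictionary includes ice_duo_cross, described as "crossover to alternate scope design/ study arm" and coded 0/1.
- **SAP section C.** "Outcomes will be compared between groups in an intention-to-treat analysis without adjustment". No per-protocol or as-treated set, sensitivity analysis or listed subgroup uses ice_duo_cross. The first output in section D, a table of variables by study group, could show crossover descriptively.

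**The concern.** The first objective is the clinical efficacy of the DEC scope against a scope of traditional design, tested for non-inferiority with a 7-point margin. If the DEC scope cannot complete a procedure and the control scope then does, that event says a great deal about how the DEC scope performs. Under scoring of the overall procedure, it enters the data as a DEC success.

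In a superiority trial, rescue that pulls the arms together is usually conservative. In a non-inferiority trial it works the other way. A worse scope has more failures available to rescue, so even an equal rescue share in both arms shrinks the observed gap. At stake is the error that the one-sided 2.5% level is meant to control: declaring DEC non-inferior when, used alone, it is worse by the full margin.

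**Working it through.** **1. The plan's own sample size.** Inputs from protocol 9.1: 92% success in both arms, margin 0.07, one-sided alpha 0.025, power 80%.

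n per arm = (1.960 + 0.842)² × 2 × 0.92 × 0.08 / 0.07² = 235.8, so 236.

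This matches the stated 236 per arm. The sample size is not in question.

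**2. Set-up for rescue.**
- The SAP gives N = 518 for the technical outcome, so n = 259 per arm.
- Assumed truth with the assigned scope alone: control 92%, DEC 85%, exactly at the margin.
- The documents give no crossover rate, so it is varied.
- The SAP names no non-inferiority test statistic. A 95% Wald bound stands in: declare non-inferiority if (pD − pC) − 1.96 × √[pD(1−pD)/n + pC(1−pC)/n] > −0.07, with observed proportions.
- The chance of that declaration is the sum of the two binomial probabilities over all outcome pairs that meet the rule (exact enumeration). Rescued failures are recoded as successes.

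**3. No rescue, or every switch scored as failure.** 2.7% (normal approximation 2.5%).

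**4. Rescue in the DEC arm only.** The scored DEC rate is 0.85 + r.

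| Points rescued (r) | Patients, r × 259 | Scored rates, control / DEC | False non-inferiority |
|---|---|---|---|
| 1 | about 3 | 92% / 86% | 6.0% |
| 2 | about 5 | 92% / 87% | 11.8% |
| 3 | about 8 | 92% / 88% | 21.4% |

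Hand check at r = 0.02: standard error = √[(0.92×0.08 + 0.87×0.13)/259] = 0.0268. Then Φ(0.02/0.0268 − 1.96) is about 11.2%, close to the exact 11.8%.

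**5. The same share s of failures rescued in both arms.** Control becomes 1 − 0.08(1−s) and DEC becomes 1 − 0.15(1−s), so the gap shrinks to 0.07(1−s).

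| Share rescued (s) | Scored rates, control / DEC | Gap, points | False non-inferiority |
|---|---|---|---|
| 10% | 92.8% / 86.5% | 6.3 | 4.9% |
| 20% | 93.6% / 88.0% | 5.6 | 8.6% |
| 25% | 94.0% / 88.75% | 5.25 | 11.3% |

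**6. Cases without inflation.** If each arm gains 1 point (93% / 86%), the rate is 2.8%. If control gains 2 points and DEC gains 1 (94% / 86%), it falls to 1.1%.

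At 236 per arm the results are similar: 5.8% to 20.0% for step 4 and 4.8% to 11.0% for step 5.

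**The case against.** **The misclassification is inferred, not stated.** No sentence says that a rescued procedure counts as a success for the assigned arm. The endpoint's opening phrase attributes success to the DEC scope, and some entries in Table 2, such as failure to cannulate or to load devices, could be applied to the assigned scope before a switch. This stands as a limit on the claim. Even so, the operative instruction is to score the whole procedure by indication, and nothing tells adjudicators to stop at the switch. Their redacted reports may not show it.

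**The direction is not fixed.** A reader might infer that the comparison is certainly biased towards non-inferiority, or reach for an extreme case such as half of all DEC failures rescued and no control failures. The documents do not support either. Section 5.4 opens rescue to both arms, no crossover rate is given, and step 6 shows that the effect can vanish or reverse.

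**Overall-procedure success is a coherent endpoint.** The 92% baseline is itself an overall procedural success rate, and the margin is set against it. A policy of starting with DEC and switching if needed is a legitimate question. But the plan never states that this is the question, and its answer does not show that the DEC scope itself performs as well. This objection is a good reason to keep the overall-procedure analysis and add to it, not to replace it.

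**Crossover is not ignored entirely.** It can be tabulated by arm. That is description only, and it does not protect the non-inferiority claim.

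**Conclusion.** The concern holds in this form. Switching is allowed in either arm, the overall procedure is scored with no rule for a switch, and intention-to-treat is the only analysis named. Followed as written, a DEC procedure completed with the control scope is scored as a DEC success. This can bias the comparison towards non-inferiority if DEC failures are rescued more often, or if a similar share of failures is rescued in both arms.

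Under the stated assumptions, about three rescued DEC patients and no rescued control patients roughly double the false non-inferiority rate, from 2.7% to 6.0%. An equal rescue share of 25% in both arms takes it to 11.3%. These figures depend on an unknown crossover rate, on true unaided rates of 92% and 85%, and on a Wald bound that the SAP does not specify. They show what is possible and do not predict what will happen.

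**What to change.** Leave the clinical choice of scope unchanged. In the SAP:

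1. State how a procedure with a scope switch is scored in the planned overall-procedure analysis.
2. Prespecify an assigned-scope analysis of technical success in which any ice_duo_cross = 1 is a failure of the assigned arm. Apply the flag in a blinded data step, because the redacted reports may hide the switch.
3. Claim non-inferiority only if this analysis and the intention-to-treat overall-procedure analysis agree.
4. Report crossovers by arm, with reasons where the procedure records give them. The 0/1 flag does not hold the reason, which is why step 2 counts every crossover.

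Do not rely on a per-protocol set that drops crossovers. It takes the device failures out of the denominator, and those are the events of interest.

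**Cost.** The change needs SAP wording and one variable derived from a flag already collected. Success rates in the assigned-scope analysis will read lower. If the 92% baseline already includes rescues, power in that analysis falls, and the SAP should say so. At 259 per arm, by the same enumeration, starting from about 83% at 92% in both arms:

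| Crossover, points | In both arms | In DEC only |
|---|---|---|
| 1 | about 80% | about 69% |
| 2 | about 76% | about 52% |
| 3 | about 72% | about 35% |

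The DEC-only column is low because the DEC scope is then truly 1 to 3 points worse when used alone.
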